#### Property Attributions task: Assessing the role of folk physics, biology, psychology, and sociology in reasoning about religious agents

The Property Attributions task is designed to evaluate conceptualizations of religious and supernatural agents [for similar tasks, see 8,38,55]. This is part of the Child Protocol; see Fig 2.

*Task design and procedure*. The Property Attributions task consists of a 20-item close-ended battery intended to assess participants’ representations of the physical, biological, cognitive-epistemic, social-emotional, and sociological properties and constraints of two to three religious/supernatural agents, as compared to the properties and constraints of ordinary human agents.

The task features the “Biggest” god [51] in the cultural-religious setting as well as 1–2 additional prominent religious agents. These religious/supernatural agents are also featured in the Sorting task (described in the previous section) and in the Justifications task (described in a later section); if a child indicates that they are not familiar with one of these agents in the Sorting Task, this agent is omitted from the Property Attributions and Justifications tasks for that child. Questions about human or human-like prophets and other agents who are not the “Biggest” god are referred to as “Agent 1” for the purposes of this task, and always precede questions about the “Biggest” god (“Agent 2”). Throughout the task, these religious/supernatural agents are compared to an ordinary human (“a person”). See Table 2 for items selected for each US sample.

**Table 2 pone.0292755.t002:** Sample-specific item selection for the Property Attributions and Justifications tasks, for the five religions included in US samples.

	Religion				
Agent	*Protestantism*	*Catholicism*	*Church of Jesus Christ of L*.*D*.*S*.	*Judaism*	*Islam*
*1*	Jesus	Jesus	Jesus	Elijah	the Prophet Muhammad
*2*	God	God	God	God^a^	Allah
*3*	the Holy Spirit	the Holy Spirit	the Holy Spirit	Jesus	Jesus

Unaffiliated children in the US are shown the version of the protocol that corresponds to the religion with which they are likely most familiar (see main text for details). See main text for descriptions of network-wide guidelines for item selection. “L.D.S.” stands for “Latter-day Saints.”

^a^ If the researcher becomes aware that the child is more familiar with the term “Hashem” or “Adonai” then the more familiar term is used in place of “God” throughout the Child Protocol.

The 20 items used in this task probe five key domains of foundational laws that govern human behavior. For each domain, half of the four items are phrased as choices between two alternatives, and half are phrased as choices between an alternative and its negation; half are phrased in the generic, present tense and half in the hypothetical, subjunctive tense; and half present the violation of the law first and half present it second.

In the *physical* domain, four items probe reasoning about the constraints of physical objects: namely, the laws of solidity (“Would [agent] need to find a door in order to pass through a wall, or could [agent] pass straight through a wall without using a door?”), continuity (“Is [agent] ever in different places at the same time, or is [agent] always in one place at a time?”), mass (“Does [agent] have a shadow, or does [agent] have no shadow?”), and time (“Could [agent] go back in time and do last week over again, or could [agent] not do that?”).

In the *biological* domain, four items probe reasoning about the constraints of biological animals: the need for food (“Could [agent] keep going without ever eating any food, or would a [agent] need to eat food eventually?”), susceptibility to illness (”Does [agent] ever get sick or does a [agent] never get sick?”), the need for sleep (“Would [agent] ever need to sleep, or would a [agent] never need to sleep?”), and the aging process (“Does [agent] stay the same age forever, or does a [agent] get older every year?”).

In the *cognitive-epistemic* domain, four items probe reasoning about the constraints of agents with limited minds: fallibility/mistakes (“Does [agent] ever make mistakes or does a [agent] never make mistakes?”), limited memory (“Would [agent] remember everything forever or would a [agent] ever forget something?”), limited knowledge (“Does [agent] know everything or does a person not know everything?”), and limited ability to read others’ minds (“Could someone trick [agent] by telling a lie, or would [agent] know that they were lying?”).

In the *social-emotional* domain, four items probe reasoning about the constraints of beings who have social and emotional lives: susceptibility to loneliness (“Would [agent] be okay if a [agent] were all alone forever, or would a [agent] get lonely?”), susceptibility to anger (“Would [agent] ever get angry, or would [agent] never get angry?”), susceptibility to worry (“Is [agent] always sure that things will be ok, or does [agent] ever feel worried?”), and susceptibility to shyness (“Does [agent] ever feel shy, or does a [agent] never feel shy?”).

Finally, in the *sociological* domain, four items probe reasoning about the constraints of beings who live in human-like social structures: kinship relations (“Does [agent] have a family, or does [agent] have no family?”), differential liking (“Does [agent] like everyone the same, or does [agent] like some people more than others?”), being part of a hierarchical power structure (“Would [agent] always be in charge no matter who else was around, or is there anyone who could tell [agent] what to do?”), and being subject to rules and norms (“Would [agent] ever have to follow any rules, or would [agent] never have to follow any rules?”

To introduce the task, the researcher tells the child, “Now I’m going to ask you some new kinds of questions. I’m going to ask you some questions about people, and I want you to think about normal, everyday people. I might also ask you some questions about others, like [Agent 1] and [Agent 2] (*if applicable*: and [Agent 3]). I might ask you about some things you said are not real, and I might ask you some questions that you think are kind of weird or silly, and that’s okay. I’m still going to ask you, and I want you to take your best guess.”

The 20 questions just described are then presented in random order. For each question, children are first asked to evaluate the human, and then the supernatural or religious agents (e.g., “Does a person stay the same age forever, or does a person get older every year? What about [Agent 1]?,” “What about [Agent 2]?,” and (if applicable), “What about [Agent 3]?”). If additional scaffolding is needed, in particular for younger children, the researcher repeats the question in full (e.g., “Does [Agent 1] stay the same age forever, or does [Agent 1] get older every year?”).

In the US samples, this task is estimated to take 4 to 12 minutes with younger participants and 8 to 13 minutes with the oldest participants.

*Adaptation for US samples*. The final set of agents featured in the Property Attributions and Justifications tasks for the five religions included in US samples is presented in Table 2.

*Parallel task for parents/caregivers*. Parents/caregivers complete a slightly modified version of the Property Attributions task. Parents/caregivers answer the same 20 questions as children and provide certainty ratings for each question on an 11-point scale ranging from [0] “Not sure at all” to [10] “Extremely sure.”

*Planned analyses*. We hypothesize that children will attribute more human-like properties to the human agent than to the supernatural/religious agents [see 8, 38, 55, 56]; i.e., that children will be more likely to endorse violations of the physical, biological, cognitive-epistemic, emotional, and sociological laws for the supernatural/religious agents than for the human. To test this hypothesis, we will examine the main effect of agent type (supernatural/religious vs. human).

We also expect that the difference between supernatural/religious and human agents will vary across domains; in particular, we hypothesize that the difference between the supernatural/religious agents and the human will be greater for violations of physical and biological laws than for violations of cognitive-epistemic, emotional, or sociological laws [56–58]. To test this hypothesis, we will examine statistical interactions between agent type (supernatural/religious vs. human) and domain (physical, biological, cognitive-epistemic, emotional, sociological).

Developmentally, we hypothesize that attributions of human-like properties to supernatural/religious agents will decrease with age [see 8, 49, 50, 55, 59, 60]. We anticipate that older children will be more likely to say that supernatural/religious agents will violate constraints, as compared to younger children; to test this hypothesis, we will examine the main effect of participant age (4–10 years), considering only supernatural/religious agents. We also anticipate that children’s perceptions of the *difference* between the supernatural/religious and the human will increase with age; to test this, we will also examine a statistical interaction between agent type (supernatural/religious vs. human) and participant age (4–10 years).

Many of these analyses will be informed by assessments of the observed reliability (i.e., internal consistency) of items within each of the five domains (physical, biological, cognitive-epistemic, emotional, sociological).

Beyond these predictions, we plan to examine higher-order statistical interactions (e.g., an interaction between type, domain, and participant age); to characterize children’s perceptions of the properties of specific agents (e.g., Jesus, God, etc.); to compare responses across samples from different cultural-religious groups; to compare children’s responses to those of parents/caregivers; to explore relationships between children’s responses in this task and information provided in the Parent Survey; and to examine relationships between this and other tasks included in the Child Protocol.

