The next set of questions within each block focuses in particular on children’s judgments about the reality status of the agent. First, the researcher asks the child to make a *reality judgment*: “Remember when we were talking about things that are real or not real? Can you remind me what you think about this: Is/are [agent] real or not real?” Then the researcher asks the child to assess their *certainty* about this reality judgment by asking, “How sure are you that [agent] is/are [child’s answer: real/not real]? A little bit sure, or really sure?” This is followed by an assessment of the child’s *source knowledge* regarding this reality judgment: “How do you know that [agent] is/are [child’s answer: real/not real]?” The final question in this set of questions is about the child’s sense of *community consensus* regarding this reality judgment: “Would most people in your [city/town/village] agree with you and say that [agent] is/are [child’s answer: real/not real]?”

Finally, the child is asked two additional questions designed to shed light on their construals of the agent: (1) a judgment about the *valence* of the agent, “Is/are [agent] good or bad?”; and (2) a judgment about the *corporeality* of the agent, “Does/Do [agent] have a body/bodies?” In contrast to other questions in the Child Protocol, researchers are encouraged *not* to press the child to make forced-choice responses to these questions; if a child gives a response like “in between” or “kind of,” the researcher instead asks, “Can you tell me more about that?”

In the US samples, this task is estimated to take 2 to 18 minutes with younger participants and 6 to 14 minutes with the oldest participants.

*Adaptation for US samples*. As described earlier, the final set of agents featured in the Property Attributions and Justifications tasks for the five religions included in US samples is presented in Table 2.

*Parallel tasks with parents/caregivers*. There is no parallel task for parents/caregivers.

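### Property Attributions pools agents the child calls real with agents the child calls not real, and on 8 of its 20 items a literal denial scores as a supernatural attribution

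*Protocol article*

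**What the plan says.** All references are to the protocol article.

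- **Filter.** In the Property Attributions task the only filter on agents is familiarity: "if a child indicates that they are not familiar with one of these agents in the Sorting Task, this agent is omitted from" this task and the Justifications task. There is no filter on reality status.
- **Script.** The child is told that "I might ask you about some things you said are not real", and then: "I’m still going to ask you, and I want you to take your best guess". The article states no opt-out for a child who thinks the agent does not exist.
- **Items.** There are 20 items, four in each of five domains. Within each domain, "half are phrased as choices between an alternative and its negation", and "half present the violation of the law first and half present it second". Half are in the generic present tense and half are hypothetical.
- **Outcome and tests.** Under Planned analyses the hypothesis is that "children will be more likely to endorse violations of the physical, biological, cognitive-epistemic, emotional, and sociological laws" for religious agents than for the human. The tests named are agent type, agent type by domain, age within religious agents, and agent type by age. None contains a reality term.
- **Reality judgement.** It is taken for each agent in the Sorting task, before this task, and again in the Justifications task: "Is/are [agent] real or not real".

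**The concern.** The outcome is meant to show that a child thinks an agent is free of human limits. For an agent the child thinks does not exist, some of the same answers are simply true. Something that does not exist casts no shadow, is never ill and has no family. An item such as "Does [agent] have a shadow, or does [agent] have no shadow" cannot tell the two kinds of child apart, and the stated tests do not separate them.

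What is at stake is interpretation. A confirmed agent-type or age hypothesis could partly reflect disbelief. Cross-sample comparisons could do so too: religiously unaffiliated children take these items, and children given the Jewish version are asked about Jesus as Agent 3.

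**Working it through.** **Step 1. Reproduce the stated design.** I coded the 20 printed items by phrasing and by position of the violation. This gives 10 items that set an alternative against its negation (2 per domain) and 10 with the violation first (2 per domain). Both match the article.

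**Step 2. Polarity of the 10 negation items.**

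| Domain | Negative answer is the violation | Negative answer is human-like |
|---|---|---|
| Physical | shadow | time |
| Biological | sick, sleep | none |
| Cognitive-epistemic | mistakes | knowledge |
| Social-emotional | angry, shy | none |
| Sociological | family, rules | none |
| Total | 8 | 2 |

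So 8/20 = 40% of all items, and 8/10 = 80% of negation items, score a bare negative as a violation.

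**Step 3. Tense.** Three of the eight (sleep, angry, rules) ask what the agent would do. The other five (shadow, sick, mistakes, shy, family) are generic present tense. Literal denial fits those five best: 5/20 = 25%.

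**Step 4. Does the order balance protect?** No. It balances position, not polarity. The violation comes second in all 8 bare-negative items. It comes first in 10 of the other 12 (all but the wall and lying items).

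**Step 5. Score of a consistently literal denier.** Take the 8 items as violations, the time and knowledge items as human-like, and let g be the assumed violation rate on the 10 two-alternative items:

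rate = 8/20 + (10/20) × g

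- g = 0: 0.40
- g = 0.5: 0.65
- g = 1: 0.90

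The article gives no value for g and no share of children who answer this way, so no sample-level figure follows.

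**Step 6. Agent type.** On the 8 items a literal denial either turns a human-like answer into a violation or leaves a violation as it was. An ordinary person is not open to the same denial. On these items the contrast can therefore only move in the hypothesised direction. On time and knowledge the movement is the opposite.

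**Step 7. Domain.** The hypothesis sets physical and biological against the other three.

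- All eight items: 3/8 = 37.5% v 5/12 = 41.7%, about 4 points and against the hypothesis.
- The five generic items, one per domain: 2/8 = 25% v 3/12 = 25%, no imbalance.
- Comparisons of single domains can differ more: 1/4 for physical or cognitive-epistemic v 2/4 for each of the others.

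**Step 8. Age, with every rate assumed.** Let literal denial rise from 10% to 30% over the age range and let other children's endorsement stay constant at 30% to 60%.

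- Negation items: (0.30 − 0.10) × (0.80 − 0.60) = 0.04, and 0.20 × (0.80 − 0.30) = 0.10. This is a spurious rise of 4 to 10 points.
- All 20 items: 0.20 × (0.40 − 0.60) = −0.04, and 0.20 × (0.90 − 0.30) = 0.12. The range is −4 to +12 points, so the sign is not fixed.

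**The case against.** The strongest reply is that the mechanism is assumed. The task is about how children represent agents, and a child can hold a concept of an agent they think unreal. The script says that such agents will come up, that this is fine, and that a best guess is wanted. That invites answers from within the concept. This stands: the documents do not show that disbelieving children answer literally. It leaves the size unknown but does not make the two kinds of answer distinguishable.

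A second reply is that the article plans to relate this task to other Child Protocol tasks and to check internal consistency, calls these its most basic analyses, and describes the protocol as largely exploratory. This lowers the severity. But the clause on other tasks is generic: it neither names reality status nor conditions any hypothesis test on it. Nor is this a detail merely left to a fuller plan, since the article itself sets the filter, script, items and terms of each test.

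Three stronger readings are tempting and are not supported.

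- **A fixed bias in points.** Any such figure needs assumed answers to the other 12 items and an assumed share of literal deniers.
- **Bias toward no difference between samples.** This needs believers to give the violation answer on these items. The article says Agent 1 includes human or human-like prophets. Where believers give human-like answers, literal denial would create a sample difference.
- **Denial rises with age.** The Sorting hypothesis is only that the gap between natural agents and fictional or supernatural agents widens, which could come from natural agents alone.

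**Conclusion.** The point holds as an interpretive weakness in the stated tests. Agents called not real are kept by design and pooled with agents called real. On 8 of 20 items (5 of them generic present tense) a literal denial and a supernatural attribution score alike. This rests on the printed items and the named test terms, and needs no assumption.

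How much it matters depends on how many children deny a familiar agent and how many of those answer literally; the article gives neither. The direction is settled only for agent type on the 8 items. For age and cross-sample comparisons it is open. The hypothesised domain contrast is barely touched. The weakness can be repaired at analysis and does not invalidate the task.

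**What to change.** Keep the pooled tests as stated. Beside them, report the agent-type, agent-type by domain and age results by the child's Sorting reality judgement for that agent (real or not real), including an estimate for agents judged real. For the agent-type results, set each group of responses against the same children's answers about a person.

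Label this supplementary. Belief may itself change with age, so restricting to agents judged real alters the developmental question and should not replace the pooled result.

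If an item-level sensitivity analysis is run, compare the 8 bare-negative items with the other 12, and state that option order is confounded with this split (violation second in all 8, first in 10 of the 12). Simply dropping the 8 would break the order balance.

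No new data are needed. The cost is fewer trials, and so less precision, in the judged-real estimate, mainly in the unaffiliated sample.

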### Research question 1: How do children represent and reason about religious and supernatural agents?

#### Sorting task: Assessing the familiarity and reality status of religious agents

Building on previous work on children’s understanding of what is real vs. not real [e.g., 49] as well as children’s ability to sort items based on some type of rule [i.e., familiarity and reality status; see, e.g., 50], the Sorting task is designed to assess children’s familiarity with natural, supernatural, and religious agents, and their judgments about which of these agents are real. This task is part of the Child Protocol; see Fig 2.

*Task design and procedure*. To begin the task, the researcher says, “We’re going to talk about a bunch of different things. Your first job is to tell me if you’ve ever heard of the thing I mention. Then, your second job is to tell me if you think the thing is real or not real. Let’s try some.”

Next, the child is presented with two practice trials in a random order. One practice trial involves a familiar agent (“doctors”), and the second practice trial involves the use of a nonsense word that children should indicate is unfamiliar (“breksters”). These practice trials are designed to familiarize children with the task format; to encourage them to use the full range of response options available to them; to encourage them to take the task seriously (i.e., provide sincere responses even if the questions seem silly or unusual); and to establish that the task will include both familiar and unfamiliar and both real and unreal agents.

Immediately following the practice trials, the child is presented with roughly 15–20 test trials in a random order. On each trial, the child is asked two questions about an agent, in a fixed order: “Have you ever heard of [agent]?” (familiarity judgment; response options: “yes” or “no”) and “Is/are [agent] real or not real?” (reality judgment; response options: “real” or “not real”).

The range of agents included in this task is intended to vary across samples to preserve cultural and religious specificity and appropriateness, within certain limits designed to maintain a balanced level of standardization across samples. The aspects that were standardized are described in the following paragraphs; see Table 1 for items selected for each US sample.

**Table 1 pone.0292755.t001:** Sample-specific item selection for the Sorting task, for the five religions included in US samples.

Religion				

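### Property Attributions task: the two age tests treat all religious agents as one class, although which agents a child is asked about can change with age and version

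*Protocol article*

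**What the plan says.** All places are in the Protocol article.

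- **Agents.** The Property Attributions task compares an ordinary person with "two to three religious/supernatural agents". "Questions about human or human-like prophets and other agents who are not the" Biggest god are labelled Agent 1; the Biggest god is Agent 2. Table 2 lists Jesus, God and the Holy Spirit for the Protestant, Catholic and Latter-day Saint versions. It lists Elijah, God and Jesus for Judaism, and the Prophet Muhammad, Allah and Jesus for Islam.
- **Omission rule.** "if a child indicates that they are not familiar with one of these agents in the Sorting Task, this agent is omitted" from this task and from the Justifications task for that child.
- **Hypothesis tests (Planned analyses of this task).** Agent type has two levels: "To test this hypothesis, we will examine the main effect of agent type (supernatural/religious vs. human". The same factor is crossed with domain and with age. For the developmental hypothesis, "we will examine the main effect of participant age (4–10 years), considering only supernatural/religious agents".
- **Familiarity.** The Planned analyses of the Sorting task predict that familiarity with the agents increases with age.
- **Related plans.** Describing specific agents and comparing samples are listed after the hypothesis tests of this task, as further analyses. The Justifications task, which uses the same agents, plans effects of agent with each agent as its own level, and agent-by-age interactions.

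**The concern.** The age hypothesis is about how children's view of religious agents changes: older children should endorse more violations of human constraints. A pooled age effect answers that only if the agents in the pool are the same at every age, or are viewed alike. The article's own design makes neither safe to assume. It distinguishes prophets and other figures from the Biggest god, asks about eating, sleeping, ageing, family and mistakes, and removes agents according to a familiarity answer that it expects to depend on age.

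If younger children are mostly asked about God, and older children about God and two human or human-like figures, the pooled rate can fall with age although nobody has changed their mind about any agent. Because the person is asked about at every age, the same drift passes into the agent-type-by-age interaction. Both developmental tests of this task are exposed. The agent lists also differ between versions, so the size of a pooled effect in one version is not on the same footing as in another. Unaffiliated US children receive whichever version is most familiar to them, so the lists can differ even within that one sample.

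**Working it through.** The article gives no figure to reproduce here, and no violation or familiarity rates. Every rate below is an assumption, shown over a range.

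**1. Weighted mean.** Let p be the chance that a violation is endorsed for an agent, held constant over age, and f the share of children who know that agent. Then

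pooled rate = Σ(p × f) / Σ f.

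God plus two prophets (order: prophet, God, prophet):

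| p | f at age 4 | f at age 10 | pooled, age 4 | pooled, age 10 | change |
|---|---|---|---|---|---|
| 0.3, 0.9, 0.3 | 0.50, 0.95, 0.30 | 0.95, 1, 0.80 | 1.095/1.75 = 0.626 | 1.425/2.75 = 0.518 | −0.108 |
| 0.4, 0.8, 0.4 | 0.50, 0.95, 0.30 | 0.95, 1, 0.80 | 1.08/1.75 = 0.617 | 1.50/2.75 = 0.545 | −0.072 |
| 0.5, 0.8, 0.5 | 0.70, 0.95, 0.50 | 1, 1, 0.95 | 1.36/2.15 = 0.633 | 1.775/2.95 = 0.602 | −0.031 |
| any of these | 1, 1, 1 | 1, 1, 1 | unchanged | unchanged | 0 |

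With equal p for all agents the change is also zero. In the second row a real rise of about 0.07 in every agent's rate would be cancelled (0.545 + 0.07 = 0.615, against 0.617 at age 4).

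**2. Interaction.** With the person fixed at 0.10, the first row gives a religious-minus-person difference of 0.526 at age 4 and 0.418 at age 10. The change is again −0.108.

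**3. Christian versions.** Under the same two familiarity patterns, with p for Jesus, God and the Holy Spirit of (0.5, 0.9, 0.9), (0.6, 0.8, 0.8) or (0.6, 0.8, 0.6), the change is −0.003 to −0.036. If only the Holy Spirit is learned late, the sign reverses. With p = 0.5, 0.9, 0.9, f = 0.90, 0.95, 0.30 when young and 1, 1, 0.90 when old, the pooled rate goes from 1.575/2.15 = 0.733 to 2.21/2.90 = 0.762, or +0.03. That drift favours the hypothesis.

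**4. Effect on the test.** Simulation: 400 runs, 90 children (inside the planned 75 to 100 per US sample), 20 items per agent, child random-intercept SD 0.5, no true age effect for any agent. The model is a binomial regression with standard errors clustered by child. Share of age tests with p < 0.05:

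| scenario | agents pooled | agent as a term |
|---|---|---|
| God + two prophets, strong familiarity gradient | 0.57 | 0.06 |
| God + two prophets, mild gradient (p = 0.4, 0.8, 0.4) | 0.16 | 0.08 |
| Christian version, Holy Spirit learned late | 0.15 | 0.06 |
| all agents known at all ages | 0.06 | 0.06 |
| all agents viewed alike | 0.06 | 0.07 |

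Monte Carlo error near 0.05 is √(0.05 × 0.95/400) ≈ 0.011. The adjusted model used one common age slope. Agent-specific slopes were not simulated, but each is estimated within one agent, so composition cannot enter.

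**5. Agent list across versions.** With everyone familiar, Jesus rated like a prophet and the Holy Spirit like God, the pooled rate is 0.50 to 0.60 for God plus two prophets. It is 0.67 to 0.70 for Jesus, God and the Holy Spirit. The gap of 0.10 to 0.20 comes from the list alone.

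**The case against.** **The agent-type contrast.** A reader might infer that the agent-type main effect is itself invalid. The documents do not support that. Every child also rates a person on the same 20 items, so the contrast is within child, and the two-level factor matches the hypothesis as stated. With 0.8 for a divine agent, 0.3 for a prophet and 0.1 for a person, it is still (0.8 + 0.3 + 0.3)/3 − 0.1 = 0.37 in the Judaism and Islam versions. Agent mix alters its size, not its direction.

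**The gap between versions.** A reader might also arrive at 0.70 v 0.37 by rating Jesus as divine in the Christian versions and as a prophet in the other two. Rated alike in all versions, the Christian figure is (0.8 + 0.3 + 0.8)/3 − 0.1 = 0.53, and the gap roughly halves. Nor does the article say that prophets become more human-like with age; it predicts the opposite for the whole class.

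**The Sorting task.** It is tempting to charge this task with the same fault, since its purpose speaks of "familiarity with natural, supernatural, and religious agents, and their judgments about which of these agents are real" while its tests use one supernatural class. But every listed agent is asked about there whatever the familiarity answer, so the mix cannot drift with age.

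**What the article already does.** It plans to describe specific agents, warns in the Discussion that comparisons across samples must allow for differences between versions, calls the protocol largely exploratory, and may leave model terms to an analysis plan not shown. All this is fair and lowers the stakes. None of it changes the age test as worded, "considering only supernatural/religious agents", or the two-level interaction with age.

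**Conclusion.** The concern holds for the two age tests of the Property Attributions task. The omission rule, the predicted rise in familiarity and a single pooled class together allow agent mix to pass for developmental change, or to mask it. Under the assumed rates the drift is about 0.03 to 0.11 from age 4 to age 10 in a God-plus-two-prophets version, against the hypothesis. It is smaller in the Christian versions, where it can take either sign. It is zero if agents are viewed alike or all are known. How large it is in practice cannot be told from the article.

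The agent-type main effect stands in direction. Its size depends on the agent list, so pooled effects should not be compared across versions without agent-specific estimates. The documents do not support a claim that the effects merely reflect which agents were asked about, nor a need to replace the pooled hypothesis by one about the Biggest god alone.

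**What to change.** 1. In the age test and the agent-type-by-age test, fit agent as a factor (person, Agent 1, Agent 2, Agent 3) with its own age slope, as the Justifications task already foresees. Carry the agent's identity by version, since the numbered slots do not hold the same figure: Jesus is Agent 1 in the three Christian versions and Agent 3 in the other two.
2. Keep the pooled contrast, and report the Biggest god v person contrast beside it. Use the latter for comparison across versions, because it is the one role common to all five.
3. Add a sensitivity analysis in children who were asked about all agents in their version, and report by age how many children were asked about each agent.

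This is a change of analysis wording and needs no new data. The cost is somewhat wider intervals for agent-specific estimates and more slopes to report. Two limits remain: each agent's slope describes children who know that agent, and the sensitivity set will lean towards older children if familiarity does rise with age.
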